### Statistical analysis

We will generate descriptive statistics for participants’ demographics, lifestyle behaviors (physical activity, tobacco use), family history of chronic disease, history of other comorbidities (e.g., hypertension, diabetes, dyslipidemia, thyroid disease), and cancer treatment-related exposures. We will assess participation bias by comparing demographics (age, gender, race/ethnicity) and treatment-related exposures among participants and non-participants. Although the number of adverse events is not the major outcome of the study, we will report any adverse events during the study intervention period. We will use a two-sided type I error=0.05. An intention-to-treat analysis will be done by including all randomized participants. We will also conduct another analysis by excluding participants that demonstrate <70% compliance rates within the telehealth exercise sessions completed (17/24). *Hypothesis 1*: The intervention will improve the SPPB test, as objectively measured using Bluetooth-enabled biosensors. We will assess changes in physical function from baseline to week 9 by using the Generalized Estimation Equation (GEE) model with an indicator variable of time, accounting for within-person correlations in measurements. Treatment by time interaction will be included in GEE and its significance tested to assess treatment effects. Body mass index, age, and race will be determined through medical records and included in GEE as a priori covariates for adjustment. Changes in physical function measures from baseline to week 9 will also be examined by a paired *t*-test (within the treatment group). A 2-sided significance level of *p*<0.05 will be used. *Hypothesis 2*: The intervention will improve a 5-scale frailty index, as measured by patient-reported questionnaires. We will assess group differences in changes in the proportion of participants who are of pre-frail or frail from baseline to week 9 using the GEE approach for proportions, accounting for correlation between measurements. As in hypothesis 1, we will include the same covariates for adjustment in the analysis. *Hypothesis 3*: Intervention-related improvements in physical function and frailty will be sustained at week 17. We will examine the long-term effects of the telehealth exercise intervention by fitting GEE models for the outcomes at weeks 9 and 17. The model will include the treatment main effect (to allow for group differences at week 17), time, and the treatment group by time interaction. Contrasts will be used to test if the group difference at week 17 equals that at week 9. As in hypothesis 1, we will include the same covariates for adjustment. Additionally, between-group differences in outcome values at week 17 will be computed, along with 95% confidence intervals, and compared to the differences at week 9. Linear mixed-effects modeling will be used to evaluate the effect of interventions over time on the primary and key secondary outcomes. The models incorporate subject-specific random effects to account for within-subject correlation due to repeated measures. Group averages, as well as subject-specific intercepts and slopes, will be estimated to capture potential variations in the baseline values and slopes among individuals. Linear mixed-effects models accommodate missing data due to dropout, such that all randomized participants can be included. We will compare participants who complete the study with those who do not and identify potential factors that are associated with dropout. An interim analysis is not currently planned for this study.

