**Methods:**

This randomized controlled trial will assess the efficacy of an 8-week telehealth exercise intervention in 60 patients with multiple myeloma who underwent autologous HSCT (30–180 days post-transplant) and are pre-frail or frail. There will be 30 intervention participants and 30 delayed controls. We will administer remote baseline assessments (week 0), followed by an 8-week telehealth intervention (week 1–8), post assessment (week 9), and an additional follow-up assessment (week 17). Our primary endpoint will be improved physical function, as assessed by the Short Physical Performance Battery test. Our secondary endpoint will be a decrease in frailty characteristics such as gait speed, strength, and fatigue. We will also evaluate the sustainability of improved physical function and frailty at week 17. Participants randomized to the intervention group will perform at least 90 min of exercise per week throughout the 8 weeks.

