**Discussion:**

This study will help optimize the delivery of safe, low-cost, and scalable telehealth exercise interventions to improve health outcomes in patients with multiple myeloma, an understudied population at high risk for physical dysfunction and frailty. Our study may provide the foundation for sustainable telehealth exercise interventions to improve physical function and frailty for other hematologic cancer patients (e.g., acute leukemia, lymphoma) as well as any other cancer population of interest.

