**Fig. 1 Fig1:**
[figure not shown]
Study flow chart. Participants are randomized into either the telehealth exercise group or the delayed control group for 16 weeks. Participants in the delayed control group are offered the same exercise program after the week 17 assessment

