After completing the 8-week telehealth exercise intervention, participants will be encouraged to continue exercising but will no longer be monitored by the exercise trainer for the next 8 weeks until the follow-up physical assessment (week 17). For participants who have successfully completed their remote physical assessments and questionnaires on Week 0 and who are randomized into the delayed control group, they will be asked to continue maintaining their current lifestyle for 17 weeks. On weeks 9 and 17, participants will complete the remote physical assessment and questionnaires again. The study staff will check in with the participants before week 17 and ask them if they would like to participate in the telehealth exercise intervention or not. The exercise program will be offered to the participants as a courtesy and is not mandatory to complete study procedures. All appropriate exercise equipment will be shipped out accordingly to those who would like to participate in the 8-week telehealth exercise program, and outcome measures will not be collected once the program is completed. The study will end after the week 17 assessment for participants in the delayed control group who do not want to participate further with the telehealth exercise option.

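### The stated adverse event window stops with the 8-week programme, leaving about half of the randomised follow-up outside it, and the arms to be counted are not named

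*Protocol article*

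**What the plan says.** The article gives adverse events one sentence, in the Statistical analysis section. It opens "Although the number of adverse events is not the major outcome of the study" and then commits to the following: "we will report any adverse events during the study intervention period". It names no arm and excludes none.

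The time frame comes from other places:

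- The abstract (Methods) puts the intervention at weeks 1 to 8, with assessments at weeks 0, 9 and 17.
- The caption of Fig. 1 gives the randomised period: "Participants are randomized into either the telehealth exercise group or the delayed control group for 16 weeks".
- The Telehealth exercise intervention section describes what follows the programme. Exercise participants are "encouraged to continue exercising but will no longer be monitored by the exercise trainer for the next 8 weeks", up to the week-17 assessment. Controls keep to their usual lifestyle and complete the same assessments at weeks 9 and 17.
- Hypothesis 3 (Statistical analysis) concerns whether gains in physical function and frailty are still present at week 17.
- The allocation is equal: "There will be 30 intervention participants and 30 delayed controls".

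**The concern.** Benefit and harm are set to be described over different periods. Efficacy is followed to week 17, but the stated harms report stops when the supervised programme stops.

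The omitted weeks matter. During the programme a trainer checks that the setting is safe at each session and changes an exercise that causes pain. Afterwards that safeguard ends, while the study still encourages exercise. Participants are pre-frail or frail and enter 30 to 180 days after transplant. The article itself foresees dizziness, injuries and falls in its safety education.

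There is also an ambiguity about arms. If the stated period means time spent receiving the programme, controls have none before week 17. If it means calendar weeks 1 to 8, controls can be counted, but with much less opportunity for events to surface. A raw comparison could then make the exercise arm look worse simply because its participants are seen more often.

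**Working it through.** The article gives no adverse event rate, count or safety margin, so there is no planned figure to reproduce. The check compares the reporting window with the randomised period and then asks what the proposed change could achieve.

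**1. Share of follow-up covered**

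- Reporting window: weeks 1 to 8, which is 8 weeks (abstract, Methods).
- Randomised period: 16 weeks (Fig. 1 caption).
- Outside the window: 16 − 8 = 8 weeks, and 8/16 = 50%.
- With 17 weeks as denominator, the span for which controls are asked to keep their usual lifestyle, 8/17 = 47%. It is about half on either count.

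**2. Person-time at full retention**

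- Covered now, if both arms are counted: 60 × 8 = 480 person-weeks (30 × 8 = 240 per arm).
- Covered to week 17: 60 × 16 = 960 person-weeks (30 × 16 = 480 per arm).

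**3. Opportunity for events to surface in weeks 1 to 8**

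- Exercise arm: 3 sessions a week × 8 weeks = 24 live video sessions.
- Control arm: no contact is scheduled between the week-0 and week-9 assessments. The staff check-in about joining the programme is placed only before week 17, without a date.
- Common to both arms: the supervised remote assessments at weeks 9 and 17.

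**4. What a longer window could and could not show (illustration with assumed event rates)**

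- With zero events among n participants, the one-sided 95% upper limit is 1 − 0.05^(1/n). For n = 30 it is 9.5%. For n = 24, which is 30 less the 20% attrition assumed in the Discussion, it is 11.7%.
- Power to compare event proportions p0 and p1 with 30 per arm and two-sided alpha 0.05 is Φ{[|p1 − p0| − 1.96·√(2·p̄(1 − p̄)/30)] / √([p1(1 − p1) + p0(1 − p0)]/30)}, where p̄ is the mean of the two.
- For 10% v 30%: p̄ = 0.20, √(2 × 0.16/30) = 0.1033 and √((0.21 + 0.09)/30) = 0.10. Then (0.20 − 0.2024)/0.10 = −0.024, so power is about 49%.
- Other assumed pairs: 10% v 20% gives 19%, 20% v 40% gives 39%, and 10% v 40% gives 78%.

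The longer window doubles the person-time described, but it does not turn this into a trial that can test safety.

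**The case against.** Several points on the other side have force.

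- **The arms.** A reader might infer that there will be no control count to compare with. The text does not support that. The sentence excludes no arm, and concurrent controls are followed over the same weeks with the same week-9 and week-17 assessments. What stands is narrower: the sentence does not say which arms are counted, and the scheduled contacts are unequal.
- **A safety conclusion.** A reader might infer from the abstract, which hopes to "optimize the delivery of safe, low-cost, and scalable telehealth exercise interventions", that the trial plans to conclude that the programme is safe. That phrase states an aim. None of the three hypotheses concerns safety, and the closing paragraph of the Discussion claims low cost and easy dissemination only.
- **Detail left to other documents.** How events are elicited and tabulated is commonly left to the full protocol or analysis plan, neither of which is shown. The article also refers to a study physician and an institutional safety board. This would answer a complaint about silence, but here the article states a window, and the window itself is too short.
- **Reporting is not collection.** The sentence limits what will be reported. It does not show that later events go unrecorded, so one cannot say that they will be missed. They are simply outside the stated commitment.
- **A deliberate choice.** The study delivers no sessions after week 8, so tying the report to delivered exercise can be defended as a preference. The reply is that the study still encourages exercise in those weeks and uses their end-point for a hypothesis about lasting benefit.

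**Conclusion.** The point holds in a limited form. As written, the reporting rule leaves out 8 of the 16 randomised weeks (50%). These are the weeks of encouraged but unmonitored exercise, and sustained benefit is assessed at their end. The rule also leaves open whether controls are counted. With 24 live sessions in one arm and no scheduled contact in the other between weeks 0 and 9, unadjusted counts would not be comparable.

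This rests on reading the intervention period as weeks 1 to 8, as the abstract defines it. If the sponsor meant the whole period to week 17 in both arms, the fault is one of wording only. No number of unreported events can be given, because the article states no event rate. The weakness lies in a descriptive, non-primary item. It does not touch the efficacy analysis, and with 30 per arm the safety information stays descriptive even after correction.

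**What to change.** Replace the sentence with one that fixes the window and the arms, for example: *Adverse events will be summarised descriptively by randomised arm from randomisation to the week-17 assessment. All participants will be asked the same questions about events at the week-9 and week-17 video assessments. Events first noted at an exercise session will be tabulated separately.*

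The separate table lets a reader compare the arms on the events that were sought equally, without losing those that surfaced at sessions.

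The cost is a few questions at two existing contacts and one more table. There are no extra visits or staff, and sample size, power and alpha are unchanged. Recall over roughly 8 weeks between assessments will be imperfect, but equally so by design in both arms. If the full protocol already collects events to week 17 in both arms, only the reporting sentence has to change.

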A total of 24 video conferences (at least 30 min/session; 3 days/week for 8 weeks) will take place in each participant’s home or remote place of choosing. Of note, the exercise time of 90min/week represents the minimum time for our intervention, and there is no upper limit. Exercise programs will be individualized and prescribed based on the participant’s baseline assessment, physical limitations, and exercise preferences. The exercise prescriptions will be developed and monitored by a clinical exercise physiologist over the course of the intervention. Each exercise session will consist of exercises targeting four essential components: dynamic balance, strength, core stability, and postural control. If a participant cannot complete the exercises as planned, the exercise trainer will provide alternative options and exercise modifications, as needed, to allow the participant to be successful and reach the desired intensity. Allocated interventions will be discontinued based on the participant’s symptoms. For example, if a participant reports any pain related to a prescribed exercise posture or ratings of perceived exertion >8, other exercise postures will be provided. Furthermore, participants will have the option to reschedule or make up an exercise session if they are unable to attend a workout on the date as planned. Exercise adherence for each participant will be captured on the Moterum platform and extracted to assess the feasibility of the prescribed exercise program.

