Although this study will provide the first evidence of a novel telehealth exercise approach targeting frailty and physical function in patients with multiple myeloma, it is beyond the scope of the current study to elucidate the mechanisms of improving frailty with exercise. Our study has the potential to demonstrate that frailty is maintained and not worsened during the intervention when compared to the delayed control group, which will be a clinically important finding. We recognize that poor retention is a possibility, given the time and effort needed to partake in an intervention study. Therefore, we have accounted for a 20% attrition rate (from randomization to week 17 post-intervention). This takes into consideration patient death, recurrence of cancer, illness, or loss to follow-up. We acknowledge that there may be differential loss to follow-up according to participant attributes and prognosis, which may contribute to participation bias and/or survival bias. To minimize participation bias, we will incorporate many of the strategies (e.g., reminders, incentives) that we have successfully used to maintain excellent participation rates in our exercise intervention studies to date. Attrition will be monitored in real time, allowing us to address obstacles in a timely manner. Differential loss to follow-up due to prognosis, death, and missing data will be addressed using statistical methods of pattern mixture models and multiple imputation. Finally, recruitment of patients with multiple myeloma can be challenging. However, our ongoing successful recruitment strategies in place for the current study, which includes collaborating with the hematology team at COH, appear to be a successful recruitment plan.

This study will provide critical evidence that contributes to the development of comprehensive telehealth exercise programs in HSCT survivors by investigating the effects of an 8-week telehealth exercise intervention in HSCT survivors with the potential of demonstrating improvements and sustainability in physical function. If successful, our approach would be low cost, easily disseminated, and have potential implications for the management and prevention of frailty in HSCT survivors as well as other cancer survivors at risk of developing frailty after cancer treatment.

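### The 70%-attendance analysis excludes patients from the exercise arm only, so it is not a randomized comparison and can show a benefit when there is none

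*Protocol article*

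**What the plan says.** The Statistical analysis section of the protocol article names two analysis sets. The first is complete: "An intention-to-treat analysis will be done by including all randomized participants". The second is additional: "We will also conduct another analysis by excluding participants". The rule in full is "excluding participants that demonstrate <70% compliance rates within the telehealth exercise sessions completed (17/24", that is, fewer than 17 of the 24 sessions.

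The section Telehealth exercise intervention shows who has sessions. The exercise arm has them: "A total of 24 video conferences (at least 30 min/session; 3 days/week for 8 weeks". Controls do not. Of those "randomized into the delayed control group, they will be asked to continue maintaining their current lifestyle for 17 weeks", some may take the programme after week 17 as a courtesy, and for that later period "outcome measures will not be collected once the program is completed". No counterpart of the exclusion rule is given for controls.

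**The concern.** Attendance is observed after randomization and in one arm only. Dropping low attenders leaves a selected exercise group against a control group that still contains the patients who would have attended poorly. Any difference between the two may reflect selection rather than exercise.

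The documents make a health-related selection plausible. The intervention section says that the allocated exercise is discontinued according to symptoms. The Discussion lists death, recurrence and illness among the reasons for attrition. A patient who declines during the 8 weeks is a natural candidate to fall below 17 sessions, and the matching control stays in. In a trial of 60 patients, a selected comparison of this kind could be read as the effect of exercise in those who did it.

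**Working it through.** **The plan's own figure.** 0.70 × 24 = 16.8, so the smallest passing count is 17 (17/24 = 70.8%; 16/24 = 66.7%). The cut-off agrees with the 70% rule.

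**Inputs from the protocol article.** SD of the function score 2.7, prior within-person correlation 0.9, assumed correlation at least 0.8, 30 per arm, 20% attrition by week 9, and a meaningful difference of 1 point (Power calculations). Two-sided alpha 0.05, with the effect tested as the treatment-by-time interaction, that is, the difference in change from baseline (Statistical analysis).

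**Assumptions not in the documents.** Share of the exercise arm below 17 sessions, 10-40%. Correlation r between attendance and recovery, 0.3-0.5. Normal scores. No true effect.

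**Closed form.** If the lowest fraction q on an attendance scale is removed, the mean change of those kept rises by r × φ(z_q)/(1−q) SDs of change. The factor φ(z_q)/(1−q) is 0.195 for q = 0.1, 0.350 for q = 0.2 and 0.497 for q = 0.3.

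- SD of change = 2.7 × √(2(1−ρ)): 1.21 at ρ = 0.9 and 1.71 at ρ = 0.8.
- q = 0.3, r = 0.3: 0.3 × 0.497 = 0.149 SD; × 1.21 = 0.18 points.
- q = 0.3, r = 0.5: 0.5 × 0.497 = 0.248 SD; × 1.71 = 0.42 points.
- q = 0.1: 0.3 × 0.195 × 1.21 = 0.07 to 0.5 × 0.195 × 1.71 = 0.17 points.

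**Null simulation.** 30 per arm, ρ = 0.8, exclusion in the exercise arm only, two-sided t-test on change as a stand-in for the unadjusted interaction test. Here r links attendance to the part of the week-9 score that baseline does not explain, with SD 2.7 × √(1−0.8²) = 1.62.

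| Excluded | Bias in points, r = 0.3 / 0.5 | Type I error, r = 0.3 / 0.5 |
|---|---|---|
| 10% | +0.10 / +0.16 | 5.5% / 6.5% |
| 20% | +0.17 / +0.28 | 6.7% / 9.1% |
| 30% | +0.24 / +0.40 | 7.4% / 12.6% |
| 40% | +0.31 / +0.53 | 9.0% / 17.3% |

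With nobody excluded, the bias is 0.00 and the error about 5%. Repeat runs move the error rates by up to about 0.6 of a percentage point.

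**Cases that weaken or reverse the bias.**

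- Attendance unrelated to function: bias 0.
- Attendance correlated 0.3 with baseline function only: the shift in change is (0.8−1) × 2.7 × 0.3 × 0.350 = −0.06 points at 20% excluded, and with 0.497 it is −0.08 at 30%. This is against the intervention, because high scorers at baseline tend to change less.
- Both links together (0.3 with baseline, 0.3-0.5 with recovery): +0.12 to +0.32 points at 20-30% excluded.
- Full overlap with attrition, where one factor drives 20% dropout in both arms and the exercise exclusion extends that to 30%: the shift is r × (0.497−0.350) = r × 0.147, which gives 0.3 × 0.147 × 1.21 = 0.05 to 0.5 × 0.147 × 1.71 = 0.13 points. The type I error is then about 5-6%.

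**The case against.** The strongest reply is that the main result is safe. The intention-to-treat analysis is stated first and keeps everyone, the attendance analysis is an extra, and nothing in the article lets it carry the efficacy conclusion. That stands. A reader might infer that the trial's principal comparison is compromised; the text does not support this.

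A reader might also infer that the rule always favours exercise. It does not: the sign depends on why sessions are missed, and the documents do not say. Nor do they say that prognosis drives attendance. The Discussion's remark that "there may be differential loss to follow-up according to participant attributes and prognosis" concerns follow-up, for which pattern mixture models and multiple imputation are planned. It makes a link with attendance plausible, no more.

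The rule could be read as excluding every control for having 0 of 24 sessions. That is strained, since compliance naturally refers to those assigned sessions.

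The exclusion share may also be small. Make-up sessions, exercise modifications, reminders and incentives are planned, and the group's previous study reported 0% attrition. This lowers the likely size but does not remove the selection.

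Finally, labelling an extra analysis as supportive is commonly left to the SAP. That is fair, and the missing label is not the point. The point is the stated rule, which if followed gives a comparison that randomization no longer protects.

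**Conclusion.** The point holds in a limited form. The attendance rule can act only on the exercise arm, so the second analysis compares a subset selected after randomization with an unselected control arm. This follows from the text and needs no assumption.

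The size does rest on assumptions. With 20-30% excluded and attendance correlated 0.3-0.5 with recovery, the spurious gain reaches about 40% of the 1-point difference that the trial treats as meaningful. Overlap with attrition shrinks it to about 0.05-0.13 points, and other attendance patterns give zero or a small negative value. A bias towards the intervention is the more plausible direction, not a certain one. The change is worth making, but the intention-to-treat conclusion does not depend on it.

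**What to change.** Replace the exclusion analysis with a complier-average effect estimated by two-stage least squares, with randomized arm as the instrument and every randomized patient kept. Missing week-9 scores need the same handling as in the intention-to-treat analysis. The preferred exposure is the number of sessions attended, with controls set to 0.

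If attendance of at least 17/24 is used as the exposure instead, state the assumption that fewer sessions have no effect. The estimate is then the intention-to-treat effect divided by the compliant share, for example multiplied by 1/0.8 = 1.25 or 1/0.7 = 1.43 when 20% or 30% fall short. It stays at zero under no effect, but it is inflated if partial attendance helps.

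If the exclusion analysis is kept, state that it applies to the exercise arm only, is descriptive, and cannot support an efficacy claim.

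The cost is a few lines of plan text and one model. The confidence interval will be wider, and the estimate relies on allocation affecting the outcome only through the sessions, plus linearity in sessions for the preferred version. It adds little to the intention-to-treat test of no effect; its use is to estimate the size of the effect under attendance.
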